## Abstract

**Background:**

Results from studies on the effects of exercise on smoking-related variables have provided strong evidence that physical activity acutely reduces cigarette cravings. Mobile technology may provide some valuable tools to move from explanatory randomized controlled trials to pragmatic randomized controlled trials by testing the acute effectiveness of exercise on quitters under real-life conditions. An mHealth app was developed to be used as a support tool for quitters to manage their cigarette cravings.

**Objective:**

The primary aim of this paper is to present the protocol of a study examining the effectiveness of the Physical over smoking app (Ph.o.S) by comparing the point prevalence abstinence rate of a group of users to a comparator group during a 6-month follow-up period.

**Methods:**

After initial Web-based screening, eligible participants are recruited to attend a smoking cessation program for 3 weeks to set a quit smoking date. Fifty participants who succeed in quitting will be randomly allocated to the comparator and experimental groups. Both groups will separately have 1 more counseling session on how to manage cravings. In this fourth session, the only difference in treatment between the groups is that the experimental group will have an extra 10-15 minutes of guidance on how to use the fully automated Ph.o.S app to manage cravings during the follow-up period. Data will be collected at baseline, as well as before and after the quit day, and follow-up Web-based measures will be collected for a period of 6 months. The primary efficacy outcome is the 7-day point prevalence abstinence rate, and secondary efficacy outcomes are number of relapses and cravings, self-efficacy of being aware of craving experience, self-efficacy in managing cravings, and power of control in managing cravings.

**Results:**

Recruitment for this project commenced in December 2014, and proceeded until May 2015. Follow-up data collection has commenced and will be completed by the end of December 2015.

**Conclusions:**

If the Ph.o.S app is shown to be effective, the study will provide evidence for the use of the app as a support tool for people who are trying to manage cravings during smoking cessation programs. It is anticipated that the results of the study will provide knowledge of how physical activity affects cigarette craving in real-life situations and inform the development and delivery of relapse prevention in smoking cessation treatment.

**Trial Registration:**

International Standard Randomized Controlled Trial Number (ISRCTN): ISRCTN55259451; http://www.controlled-trials.com/ISRCTN55259451 (Archived by WebCite at 
http://www.webcitation.org/6cKF2mzEI)

## Introduction

Although smoking cessation treatments such as behavioral support, nicotine replacement therapy (NRT), and pharmacological treatment have been effective in the short term, the long-term relapse rates are high. The percentages of relapse are between 95% for the cold turkey method and 75% for combined therapies of counseling and pharmacotherapy [1-3]. A systematic review of the effectiveness of smoking relapse prevention [4] indicates that the most effective long-term methods in preventing relapses are self-help materials. Different types of pharmacotherapy showed varied results from short-term to long-term effectiveness and behavioral interventions for relapse prevention appeared effective in the short-term only. The skills approach to behavioral intervention has been widely studied as a method with promising results [5]. Nevertheless, there is no strong evidence to support any specific behavioral intervention as being most helpful to avoid relapses after quitting smoking and there is little research available regarding other behavioral approaches [6]. The latest efforts to develop a taxonomy of behavior change techniques, used in interventions in general [7] and more specificly in smoking cessation interventions [8-10], are expected to help develop stronger evidence in future research in this field.

Exercise has recently been incorporated as a smoking cessation aid into existing programs with promising results. In general, studies examining the effects of exercise on variables related to smoking cessation have focused on either the long-term effects after long interventions or on the acute effects of exercise on smoking-related variables. A recent review [11] of exercise interventions for smoking cessation revealed mixed results. The heterogeneity of the studies reviewed did not allow credible conclusions to be drawn. They focused more on studies that provided data for long-term effects (ie, follow-up data collection at more than 6 months). Within that focus, they identified 15 trials, 3 of which showed significantly higher abstinence rates in a physically active group versus a control group at the end of treatment [12-14]. One of the studies also showed a significant benefit for exercise versus control on abstinence at the 3-month follow-up and a benefit for exercise at the 12-month follow-up [13].

The main reason for relapsing is the craving that smokers experience. Results on the effects of exercise on smoking-related variables have provided strong evidence that physical activity acutely reduces cigarette craving [15-17]. Fourteen reviewed studies that compared a bout of exercise with a passive condition or compared 2 intensities of exercise concluded that even relatively small doses of exercise should be recommended as an aid to managing cigarette cravings and withdrawal symptoms [15]. The results of 12 reviewed studies were similar, showing that cigarette craving was reduced following exercise with a wide range of intensities, from isometric exercise and yoga to activities with heart rates as high as 80%-85% [16]. Using individual participants’ data from 17 studies, participants’ engagement in physical activity was compared to that of control group participants. The results showed that the effects of all primary studies were in the same direction, with physical activity groups showing a greater reduction in cravings compared with controls, implying strong evidence that physical activity acutely reduces cigarette craving [17].

Evidence of the positive effects of exercise on acute reduction of cravings from experimental laboratory-based studies is strong [15-18], but findings are limited by a lack of long follow-up and artificial settings. Therefore, there is a need to start experimenting with interventions in real-life situations. One effort in this direction is a recent study that used a lab-based scenario with high ecological validity to show that an acute bout of exercise can reduce cravings following concurrent stressors [19]. Similar attempts to collect data from real life for smoking and exercise behavior using ecological momentary assessment methods (EMAs) have also been observed in the recent literature [20-21]. However, the investigation of the effects of short bouts of exercise as a means to acutely manage cravings in real life and the long-term effects of this method on relapse rates has not yet been the focus of any study. Our approach is similar to EMA methods in that it offers real-time data, but it differs in that entries are self-initiated and in how the app also acts as an intervention by offering suggestions to overcome craving and supportive motivation messages. The growing use of mobile technology may provide some valuable tools to move from explanatory randomized control trials that test the acute efficacy of exercise on abstinent smokers under highly controlled conditions to pragmatic randomized control trials that test the acute effectiveness of exercise on quitters under real-life conditions.

Mobile technologies are a means for providing individual-level support to health care users and a promising platform for health interventions [22]. Behavioral intervention technologies offer promising opportunities to expand psychological practice [23]. Several mobile health interventions have been designed to increase healthy behavior (eg, to promote smoking cessation or increase activity levels) and are also cost effective [24]. A review of mobile phone-based interventions for smoking cessation revealed only 4 trials: 2 using SMS text messages and 2 using the Internet and mobile phones. The trials were heterogeneous. However, when the data from both programs were pooled, they found statistically significant increases in both short- and long-term self-reported quitting [25]. A more recent systematic review [26] concluded that SMS-based smoking cessation interventions more than doubled biochemically verified smoking cessation at 6 months. Moreover, the self-help methods have been indicated in previous literature as effective for long-term effects [4] and the use of mobile phone applications as a self-help method sounds promising.

Therefore, a mobile phone application has been developed for the needs of this study. The aim of the app is to support quitters in managing their cigarette cravings and abstaining over the long term by using exercise as the main behavioral substitution strategy. The mHealth app called “Physical over Smoking (Ph.o.S)” includes a data collection mechanism to collect real-time data regarding relapses. The Ph.o.S app was developed based on evidence-based practices for relapse prevention after smoking cessation. Following that, a trial has been designed to test the effectiveness of the mHealth app.

### Trial Aim

The aim of this study is to present the protocol of a study that assesses the effectiveness of the Ph.o.S app, which helps abstaining users to manage their cigarette cravings. The study will examine the quit rates of abstaining users of the app versus the quit rates of a comparator group for a 6-month period after quitting smoking. The trial’s main hypothesis is that users of the Ph.o.S app will have higher 7-day point prevalence abstinence rates during the follow-up measures in comparison to the comparator group (trial registration number ISRCTN55259451).

Four additional hypotheses have been proposed:

Users of the Ph.o.S app will have fewer self-reported relapses during the follow-up measures than the comparator group will.Users of the Ph.o.S app will report higher self-efficacy from being aware of experiencing cravings than the comparator group will.Users of the Ph.o.S app will report higher self-efficacy in managing cravings in relapse situations than the comparator group will.Users of the Ph.o.S app will report a higher power of control to manage cravings in everyday situations than the comparator group will.

### Trial Design

This study is a 2-armed randomized clinical trial. Participants identified as eligible and who give their consent to participate will receive a smoking cessation program consisting of 3 group sessions (once per week). After the quit day, participants will be randomly assigned to 2 groups. Both groups will have a separate fourth session where they will receive training on relapse prevention and a plan to cope with cravings. The intervention group will receive an additional short training session on how to use the Ph.o.S app as an additional support tool whenever they experience cravings in their everyday life during the follow-up period. Preintervention, postintervention, and 6-month follow-up assessments will be conducted. Table 1 displays an overview of the study’s timeline and the schedule of enrollment, interventions, and assessments. Multimedia Appendix 1 displays the detailed measurement time points for each group.

**Table 1 table1:** Study timeline: overview of schedule of enrollment, interventions, and assessments.

Timeline points	Schedule				
	Screening for eligibility	Intervention: quit smoking (3 sessions)	Quit day: allocation	Intervention: manage cravings (4th session)	Follow-up assessment
-*t* _3_	X				
-*t* _2_		X			
-*t* _1_		X			
*t* _0_			X		
*t* _1_				X	
*t* _2_ (3 days after)					X
*t* _3_ (1 weeks after)					X
*t* _4_ (2 weeks after)					X
*t* _5_ (3 weeks after)					X
*t* _6_ (4 weeks after)					X
*t* _7_ (12 weeks after)					X
*t* _8_ (24 weeks after)					X

## Methods

### Study Setting

The study setting is the Jyväskylä Community Primary Health Care Center in Central Finland.

### Eligibility Criteria

All interested participants are screened for eligibility by completing a short battery of questions online. Noneligible participants are advised to contact their doctor or nurse for help. Participants are adults (between the ages of 18 and 65) who have been smokers for at least 1 year and who smoke more than 10 cigarettes per day. (Those who use snus only are excluded.) They should have no other addictions (ie, alcohol, prescription drugs, or illegal drugs) according to the behavioral screening tool NIDA Quick Screen V1.0 [27]. Eligible participants should be addicted to nicotine, with a score of more than 4 out of 10 on the Tobacco Dependence Screener (TDS) [28]. TDS is a 10-item self-report questionnaire, and it generates a continuous dependence score. It demonstrates acceptable reliability in different samples as well as validity because it has a high association with smoking heaviness measures (eg, number of cigarettes smoked per day, carbon monoxide levels) and years of smoking [28-29]. Participants should have a strong motivation to quit and score more than 3 out of 7 on the Motivation to Stop Smoking Scale (MTSS) [30]. The MTSS is a single-item scale assessing an individual’s motivation to quit smoking, combining aspects of desire and intention to quit. Scores range from 1 (I don’t want to stop smoking) to 7 (I really want to stop smoking and intend to in the next month). Participants are also screened for active psychological distress by completing the 12-item General Health Questionnaire [31] and those scoring more than 20 out of 36 are excluded [32,33] because they have lower quit rates [34,35]. Participants are screened for health risks if they increase their physical activity by completing the Physical Activity Readiness Questionnaire [36]. (Those answering yes to any question will be excluded.) Nevertheless, participants who were able to provide permission to exercise from their doctor were accepted to the program. For example, if their blood pressure, heart condition, or bone or joint problem is well controlled with drugs and their doctor says it is safe to exercise.

Finally, the Gold Standard Monitoring Form used by the National Health Service in the United Kingdom is completed for each participant [37]. The form records useful information regarding participants’ personal details, information about the type of intervention, any pharmacological support (eg, NRT, varenicline), use of other nicotine products (eg, snus), and the outcome. Participants currently trying to quit or taking a smoking cessation medication (eg, NRT, wellbutrin, or varenicline) or receiving any other form of treatment (eg, Web-based, app-based, or other) are not excluded as long as they agree to follow our methods.

### Recruitment, Randomization, and Allocation

Recruitment will occur through referrals from the health care units in the Jyväskylä area as well as via the Web pages of Central Finland Respiratory Association, the City of Jyväskylä, Radio Jyväskylä, and Yle News. All interested participants will be screened for eligibility. The enrollment period ended in May 2015. The first 50 eligible participants will start the smoking cessation intervention, which consists of 3 weekly counseling sessions and will help them set a quit date. The rest of the eligible participants will be put on a waiting list and invited to participate in case of dropouts before the quit day/randomization time point. The first 50 participants to reach the quit day/randomization time point will then form the intention-to-treat group that will continue in the study. After the quit day/randomization, participants will be assigned to an experimental group (25 participants) and a comparator group (25 participants), and both groups will separately have 1 more counseling session on how to manage cravings. In this fourth session, the only difference in treatment between the groups is that the experimental group will have an extra 10-15 minutes of guidance on how to use the Ph.o.S app to manage cravings during the follow-up period. Both groups will be followed up for the main and secondary efficacy outcomes of interest for 6 months. The method of randomization is a set of numbers generated by online software [38]. The principal investigator will generate the allocation sequence and the study nurse will assign participants to the groups. The study nurse is blind to the allocation sequence until the third session and the principal investigator is blind to the participants and their data up to the first follow-up measure.

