### Interventions

#### Smoking Cessation and Relapse Prevention Interventions

The presentation of the smoking cessation intervention content has been based mainly on the taxonomy of behavior change techniques in interventions [7] and the taxonomy of behavior change techniques used as support for smoking cessation [39]. The theoretical frameworks that the techniques are based on are control theory [40], the social-cognitive theory [41], the theory of planned behavior [42], and the motivational interviewing technique [43]. During the first session, baseline data are collected and then a group or individual motivational interview session takes place for about an hour, aiming to motivate participants to take further responsibility for making important health-related behavior changes (ie, to gradually decrease smoking and be more physically active). During the second session, participants discuss the barriers for behavior change and they brainstorm facilitators to apply. In the third session they set specific goals and make plans for behavior change. In this meeting, participants also set a quit day and they get training on the use of pedometers. The 3 sessions are scheduled weekly. The intervention is a shorter version of a previously effective intervention named “No more smoking! It’s time for physical activity” [44-45]. Multimedia Appendix 2 contains a more detailed overview of the contents of the intervention used to help participants quit smoking.

All sessions are delivered by the study nurse, who has previous experience with counseling smokers to quit. Multimedia Appendix 3 presents the content of the fourth session that covers relapse prevention, which is held for the participants within 1 week after their quit day. The aim of this fourth session is to help participants develop a cravings management plan to prevent relapses. Similarly, the presentation of the fourth session’s content has been based on the taxonomy of behavior change techniques used as support for smoking cessation [39] and in general interventions [7]. The theoretical frameworks that the techniques are grounded in are the relapse prevention model [46,47], control theory [40], social-cognitive theory [41], and the theory of planned behavior [42].

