### Data Collection Procedure

Screening data at time point -*t*
_3_ will be collected via an online questionnaire to determine eligibility for all participants who respond via the various recruitment strategies. The questionnaire consists of a short overview of the aim of the study and questions regarding the person’s addictions, quitting history, willingness to quit, general health, and readiness for physical activity. The website used to assess eligible participants is a safe and secure site called Fluid Surveys. People who are eligible, based on the online assessment, receive a follow-up telephone call from the study nurse to verify eligibility and will be invited to come to the health center to complete the consent to participate and the baseline measures.

Baseline data and behavioral and psychological self-reported data at time points -*t*
_2_, -*t*
_1_, and *t*
_1_ will be collected during the first, third, and fourth sessions of the smoking cessation intervention in a paper-and-pencil format, administered by the study nurse in a quiet area of the unit. Follow-up data at all follow-up time points (*t*
_2_-*t*
_8_) will be collected via online questionnaires after an invitation from the research assistant to participants, via email or SMS, to complete the questionnaires. In addition, data from the phone app users (experimental group only) will be collected during the follow-up period. Users’ phone data will be uploaded daily to a secure university server reserved for this purpose.

Once participants have participated in the final meeting, the researchers will make every reasonable effort to follow the participant for the entire follow-up period of 6 months. Participants may, however, withdraw from the study for any reason at any time. However, early discontinuation of Ph.o.S app for any reason is not a reason for exclusion from the study.

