### Consent

All eligible participants are given a copy of the information sheet and informed consent form to read. The information sheet provides a summary of the research study and the informed consent document states what the individual is about to participate in, the individual’s rights as a research participant, and information about confidentiality. The study nurse explains all aspects of the study and answers all of the participant’s questions regarding the study. If the person chooses to participate in the study, that person will be asked to sign the informed consent form. No study procedure is performed prior to signing the informed consent form. Subjects who refuse to participate or who withdraw from the study are treated without prejudice. The reason for refusal or withdrawal will be noted on the form if reported.

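### As worded, the study nurse's blinding to the allocation sequence ends at the third session, before quit-day randomisation, so the stated procedure does not protect allocation concealment

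*Protocol article*

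**What the plan says.** All references are to the protocol article.

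- **Who generates and who assigns** (Recruitment, Randomization, and Allocation): "The principal investigator will generate the allocation sequence and the study nurse will assign participants to the groups".
- **When the nurse's blinding ends** (same section): "The study nurse is blind to the allocation sequence until the third session". The principal investigator is said to be blind to participants and their data until the first follow-up measure.
- **When allocation happens** (Trial Design): "After the quit day, participants will be randomly assigned to 2 groups". Table 1 puts allocation at t0, together with the quit day.
- **What happens in the third session** (Smoking Cessation and Relapse Prevention Interventions): "In this meeting, participants also set a quit day and they get training on the use of pedometers".
- **Who enters the randomised set** (Recruitment, Randomization, and Allocation): "The first 50 participants to reach the quit day/randomization time point will then form the intention-to-treat group". People on a waiting list replace those who drop out before that point.
- **The nurse's other roles**: "All sessions are delivered by the study nurse, who has previous experience with counseling smokers to quit" (Interventions). After online screening, eligible people "receive a follow-up telephone call from the study nurse to verify eligibility" (Data Collection Procedure). Before consent, "The study nurse explains all aspects of the study and answers all of the participant’s questions regarding the study" (Consent).

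**The concern.** Concealment means that whoever can influence a participant's entry does not know the coming assignment until entry is irrevocable. Here the article names a time of disclosure, and that time falls before randomisation. The person to whom the sequence is disclosed has by then counselled each participant over three weekly sessions, and so has a view of who is likely to stay abstinent.

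Statistical Methods relies on intention-to-treat to keep bias out of the group comparison. Intention-to-treat preserves the groups as assigned. It cannot repair an assignment that was influenced by prognosis. With 25 per arm, very few such assignments would be needed to matter.

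**Working it through.** The article gives no figure to reproduce on this point. The check is of the order of events, followed by one illustrative calculation.

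**Order of events**

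| Step | Time point | Nurse's knowledge of the sequence | Source |
|---|---|---|---|
| Online screening, telephone check of eligibility | -t3 and after | Blind | Data Collection Procedure |
| Consent and first session | -t2 | Blind | Data Collection Procedure; Consent |
| Third session, quit day set | -t1 | Blinding ends | Recruitment, Randomization, and Allocation; Interventions |
| Quit day, first 50 to reach it are randomised | t0 | Not blind | Table 1; Trial Design; Recruitment, Randomization, and Allocation |
| Fourth session, held separately by arm | t1, within 1 week of the quit day | Must know the arm | Interventions |

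Data Collection Procedure ties -t2, -t1 and t1 to the first, third and fourth sessions. Since the quit day is set in the third session, allocation at or after the quit day follows that session. Disclosure at -t1 therefore precedes allocation at t0.

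**What is still open between -t1 and t0**

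1. The quit date, which is chosen in a session that the nurse runs.
2. Whether the participant reaches the quit day and is among the first 50. The Abstract goes further and makes success in quitting the condition for allocation.
3. Whether a dropout is replaced from the waiting list.

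**How the list might be used.** The article says only that a set of numbers comes from online software.

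- If the list is used in order of arrival, the nurse could foresee the next assignment.
- If it is keyed to code number, there is no next slot to steer towards. The participant's arm would still be known before entry to the randomised set is settled.

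**Size, as an illustration.** The arm size is 25 (Recruitment, Randomization, and Allocation). Suppose one participant with probability a of 6-month abstinence changes places with one in the other arm who has probability b. One arm's expected rate rises by (a − b)/25 and the other's falls by the same amount:

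shift = 2 × (a − b)/25 = 8 × (a − b) percentage points.

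- With perfect prediction, a = 1 and b = 0, so the shift is 1/25 + 1/25 = 2/25 = 8 points.
- With no ability to predict, a = b and the shift is 0.

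The range per exchange is thus 0 to 8 points. The Power section gives two figures for comparison: a difference of interest of 10 points, and a stated detectable difference with 50 participants of 59% − 25% = 34 points.

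**The case against.** Several points can fairly be made for the plan.

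- **Loose wording.** The third session is the last one that both groups share, and the same nurse must know the arms to hold the fourth session separately. The phrase may simply mark that boundary. This is possible, but the sentence as it stands puts disclosure before randomisation and would still need correcting.
- **Enrolment is protected.** A reader might infer that the nurse knew the sequence while enrolling participants. The article does not support that. Each participant's eligibility check and consent come before that participant's third session, when the nurse is still blind, and the entry criteria are mostly questionnaire cut-offs. Later or waiting-list entrants would be exposed only if the whole list were opened once, at the third session of an earlier cohort, and the article does not say so.
- **No slot rule is stated.** A reader might also infer that order of arrival at the quit day decides the slot on the list. The article says only that it decides who enters. This objection stands, so foresight of a next assignment remains conditional.
- **The window is short.** No scheduled contact with the nurse is described between the third and fourth sessions. That limits the opportunity, but the quit date is set inside the third session itself.
- **Unseen material.** The CONSORT checklist and the detailed timeline are appendices that are not shown, and a release procedure may be described there. That lowers confidence that no safeguard existed. It does not remove a timing that the article itself states.
- **The 8-point figure.** It requires perfect prediction of 6-month status, so it is a ceiling for one exchange and not an expected bias. It is also small beside the 34-point difference that the trial says it can detect.

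**Conclusion.** The point holds as a defect in the stated procedure. The nurse's blinding ends at -t1 and allocation is at t0. The person no longer blind helps set the quit date and makes the assignments, and entry to the randomised set is still open in between. This is a stated rule, not detail left to a fuller document.

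The documents do not support the stronger conclusion that allocation was in fact unconcealed for every participant, or that any assignment was influenced. How far an assignment could be foreseen depends on how the list is keyed and on whether it was opened all at once or one participant at a time. Neither is stated.

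The size cannot be estimated from the article. The bound is 8 percentage points per exchange between arms of 25, reached only if 6-month status is predicted perfectly.

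**What to change.** **If any allocation remains.** Change the sentence in Recruitment, Randomization, and Allocation so that the principal investigator, who already generates the sequence and is blind to participants, keeps it. Each assignment should be released singly, against a code number, only after the participant is logged as having reached the quit day and before the fourth session. The cost is one message or sealed envelope per participant and no extra staff.

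**If allocation is complete.** This is the likelier case, since recruitment ran until May 2015 and follow-up has begun.

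1. Report when and how the nurse saw the sequence, whether as a whole list or one assignment at a time, and how the list was keyed.
2. Do not describe allocation as concealed if the sequence was seen before the quit day.
3. Add a sensitivity analysis of 6-month abstinence adjusted for baseline MTSS, TDS score and cigarettes per day, all taken from the eligibility screen. Name these three in advance instead of leaving them to the preliminary analyses that Statistical Methods uses to choose covariates. MTSS belongs in the set because motivation is what a counsellor would most readily judge.
4. State that adjustment cannot remove selection on the nurse's unmeasured impressions. The disclosure in items 1 and 2 is therefore the essential part.

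The cost is a few sentences in the report and one additional model.
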